#### **4.6 Outcome Measures and Timelines**

Data collection will occur in three main areas, which are detailed below: (1) Physical and mental health (including substance use); (2) Psychosocial determinants of health and consequences of change; and (3) Cross-sector administrative data and cost outcomes. Unless otherwise indicated, data collection will occur at baseline and every six months for two years. A number of instruments are suggested in the following sections but will not be finalized until after discussion with the National Team. The focus will be on instruments that are used internationally and have sound psychometric properties. Please see Addendum B for a copy of all proposed instruments.

#### 4.6.1 Physical and Mental Health

Mental health symptoms and severity (including substance use and all Axis I and II diagnoses) will be assessed using the Symptom Checklist (SCL-90) and the MINI or the Psychiatric Diagnostic Screening Questionnaire (PDSQ). Other instruments suggested for the assessment of substance dependence/abuse include the Global Appraisal of Individual Needs (GAINS) – Substance Problem Scale, the Diagnostic Interview Schedule (DIS) and the Opiate Treatment Index. Adverse events, stress, and trauma symptoms are additional variables of interest and could be measured using the START Outcome Scale, Childhood Trauma Questionnaire and/or Adverse Childhood Events Scale, and the Trauma Symptom Checklist-40.

Given the known high mortality and the dearth of data regarding physical health conditions among people who are homeless, 20% of participants (a random sample of 20 per group, for a total of 100) will be accompanied by peer researchers to a research office at St. Paul's Hospital where physical assessments will be coordinated. If participants are in treatment or have received a recent physical examination, we will ask the participant for permission to access relevant details from their health record. The specific assessments and timelines proposed for physical health examinations are summarized in Table 1. If a participant in any treatment group is identified as having a medical condition that is in need of treatment, appropriate referrals will be made. Participants will receive an honorarium of \$50 for each physical examination.

**Table 1. Proposed Physical Health Assessments and Timelines**

| Physical Health Assessments                                                                                                                                             | T-1
(Inclusion) | T0 (Intake,
Assignment) | T1 (+6) | T2 (+12) | T3 (+18) | T4
(+24) |
|-------------------------------------------------------------------------------------------------------------------------------------------------------------------------|--------------------|----------------------------|---------|----------|----------|-------------|
| Opiate Treatment Index                                                                                                                                                  |                    | X                          | X       | X        | X        | X           |
| Chronic Health Scale                                                                                                                                                    |                    | X                          | X       | X        | X        | X           |
| Physical exam [subsample] including electrocardiogram, X-Ray, MRT, derma exam, basic blood work, infection screen (HIV, HCV, STD), basic urine toxicology, TB skin test |                    | X                          |         |          |          | X           |

#### 4.6.2 Psychosocial Determinants and Consequences of Change

Both qualitative and quantitative data will be collected through three core methods: semi-structured interviews, surveys/questionnaires and focus groups. The initial data will be largely descriptive. Over time, it will be possible to collect longitudinal data from health professionals, service and housing providers and clients. Whenever possible, data collection procedures will be triangulated to ensure accuracy and validity (e.g., base rates). All interviewers will be trained to administer the survey instruments in a consistent and standardized manner.

##### 4.6.2.1 Surveys and Questionnaires

The survey instruments consist of previously validated measures recommended by the National Project Team. We have also proposed a number of additional relevant measures. Copies of instruments are presented in Addendum B. Please see Appendix 5.0 for a summary of the timing of administration.

Housing status over the preceding 6 months will be determined at baseline and at the time of each follow-up interview using the Housing Timeline Follow-Back Calendar (HTFBC). The primary outcome variable will be housing status at the time of the 2 year follow-up interview, defined as being either: (1) Homeless, or (2) Stable Housing (living for a continuous period of at least 90 days in a house,

 The SOS is based on the core of the modified Overt Aggression Scale (see Addendum for a copy of this instrument).

apartment, SRO hotel, rooming house, or any other place of one's own for which one pays rent; Ontario MCFS, 2004). Other outcome variables to be derived from the HTFBC will include: (1) housing status at each follow-up period; (2) number of housing transitions over the previous 6 months; (3) number of nights spent homeless over the previous 6 months. The Housing Quality Score will be used to determine self-reported quality of current living conditions in terms of comfort, safety, spaciousness, privacy, friendliness and overall quality.

Demographic characteristics will be collected using subsections of the Community Mental Health Evaluation Initiative (CMEI). Quality of life will be assessed using two instruments: (1) The Quality of Life for Homeless & Hard to House Individuals (QOLHHI) Instrument (Hubley & Palepu, in preparation); and (2) the EuroQol (EQ5D), a standardized health-related quality of life instrument that generates a composite score reflecting the preference value associated with a given health state, and a global rating of current health using a visual analog scale. General functioning will be assessed using the Multnomah Community Ability Scale (MCAS). Resiliency will be assessed using the 3-item Sense of Coherence Scale. Vocational outcomes will be assessed using a timeline follow-back interview from the Montreal IPS study (indicated by MHCC), which examines work status and various details of work (e.g., setting, timing, hours, compensation, etc.).

The Sarason Social Questionnaire (SSQ-Short form) will be used to measure perceived number of social supports and satisfaction with available social supports. Family history and critical life events will be assessed using items developed by Roy et al. for the Montreal Street Youth Cohort Study. The Objective Social Outcomes Index (SIX) will be used to assess social outcomes related to mental illness.

#### **4.6.2.2 Semi-Structured Interviews**

We propose to interview individual participants and, where possible, services providers, and health professionals in relation to our hypotheses. Interviews will be in-person or by telephone. A draft interview protocol will be developed in collaboration with the local/national team and will be pilot tested with clients to ensure clarity, appropriate length, inter-rater reliability and lack of redundancy. Experienced graduate students and/or service providers or peer interviewers will conduct the interviews. This component of the data collection should take about 90 minutes to complete.

**Personal Stories:** Following the baseline quantitative interviews, study participants will be invited to participate in a second set of interviews that will focus on their life story. Approximately 10 participants from each study "arm" will be randomly selected to participate in semi-structured interviews that will address personal experiences with homelessness and mental illness. An equal distribution of men and women will be attempted (20 from the moderate needs group and 30 from the high needs group).

Two personal life story interviews will be conducted. The first interview will take place approximately 30 days after the participant entered the study and will focus on particular events, memories or episodes in their lives (one high point, one low point, one turning point) that occurred prior to and in the early stages of their participation in the study. The second interview will take place 18 months later and will focus on specific experiences related to their housing, support and clinical services. For participants who have been randomized to one of the intervention groups, questions will focus on their experiences with service providers and will include seeking permission to also interview their service providers. For participants who have been randomized to one of the TAU groups, a parallel set of questions will focus on their experiences with community service providers.

Interviews will be conducted by graduate students or service providers paired with a peer interviewer. During the interviews, respondents will be encouraged to address each topic in their own way and using their own words. This approach is essential for obtaining valid data on potentially sensitive issues by facilitating rapport between interviewer and participant. An open-ended approach allows participants to introduce substantive topics not considered by researchers (Berg 1995). Interviews will last approximately two hours and, with permission, will be recorded for full transcription and analysis. If participants refuse permission to record, researchers will take detailed notes during the interview. An honorarium of \$50 will be provided for participation.

Qualitative interviews and focus groups will be conducted to illuminate issues regarding individuals' experience of homelessness and service provision. Interviews will be conducted with a subset of randomly selected participants, staff, and other key stakeholders as outlined in the RFP.

#### **4.6.2.3 Focus Groups**

It is important to examine group perspectives on homelessness. Focus groups will be used with subsets of participants, service providers and key stakeholders to gain a better understanding of homelessness, mental illness and service provision/utilization. We propose an annual focus group with clients randomly selected from each housing/treatment condition. Each group will begin with an introduction followed by a discussion about participants' behavioural intentions for dealing with psychosocial issues. A facilitator and a recorder (trained collaborators or graduate students) will lead each group. Key points will be recorded on flip charts and audio-taped for in-depth analysis. The facilitator and recorder will meet before and after each session to ensure quality and consistency.

**Planning & Proposal Development:** Data will be gathered in the following areas via focus groups, key informant interviews, and review of program planning documents: (a) Planning processes; (b) Principles and values guiding the planning process; (c) Planning actions, and (d) Stakeholder relationships. This data will be gathered by graduate research assistants during the recruitment and baseline data gathering phase (Sept/09 – March/10).

**Implementation Phase:** Data will be gathered from key stakeholders in the housing and clinical components of the project in the following areas: (a) Implementation processes; (b) Principles and values guiding the implementation process; (c) Implementation actions; and (d) Stakeholder relationships. Data collection will include focus groups, key informant interviews, and review of program planning documents after the project has been running for one year (September 2010).

#### **4.6.3 Cost Outcome Analyses & Administrative Data**

All study participants will be asked to provide consent for the research team to utilize their personal identifiers (i.e., name, date of birth, personal health number) to obtain administrative data reflecting their health care utilization (hospital, physician services, prescriptions), social services utilization (income assistance, disability and unemployment benefits) and criminal justice encounters (arrests and Provincial sentences). The research team at CARMHA has extensive experience collaborating with government agencies in the linkage and analysis of these data. The costs associated with service events have been established through previous studies by CARMHA and the Provincial Government, and will be the basis for econometric analyses in the current study.

Data will be sought retrospectively to 1996, enriching our understanding of the trajectories of service utilization preceding study participation. These data will be refreshed and updated each year through

the active study period (2009-2013), and then bi-annually until 2019. Funds to support research following the study period will be sought separately.

#### **4.6.4 Additional Outcomes of Interest**

The core data collection will be leveraged for other outcomes of interest. Participating service providers and health professionals will be asked to complete the Health Professionals' Attitudes to Homeless Inventory (HPATHI) which assesses comfort/attitudes, interest, and confidence of health professionals in work with homeless and at risk persons.

Employment and income assistance trajectories will also be examined over time, with particular attention paid to the experiences of women. These will be important outcome measures given their contribution to individual self-sufficiency and housing stability.

#### **4.7 Good Clinical Practice**

As an RTC, by design, we are obliged to comply with the Guidelines for Good Clinical Practice (GCP; 1996), an international ethical and scientific quality standard for designing, conducting, recording and reporting trials that involve human subjects. Components of GCP are addressed at various points throughout this application; however, a thorough review of GCP, including Standard Operating Procedures, training, reporting, external audits, will need to be developed for all three intervention conditions as well as the TAU group outside the scope of this application.

#### **4.8 Data Integrity and Management**

All data will be retained in established, secure data facilities created at CARMHA at the downtown campus of Simon Fraser University. Data collection infrastructure will be provided by a professional information systems vendor and will include equipment for field data collection, secured mechanisms for transmission and processes for quality control. Protocols for data security and integrity are maintained by CARMHA and would be extended to include the data gathered from this study.

- Processes for the involvement of consumers as co-investigators and interviewers
- Partnerships with multiple Provincial Ministries, health agencies, and non-profits in order to gather, maintain, and analyze primary data and linked administrative data
- On site facilities for secure data input, verification, archiving, back-up, analysis
- Expertise on site to design and direct chain of custody for all data, sharing with relevant investigators in Vancouver and the National team

We will also develop additional resources for key operational tasks, including data collection and entry (graduate research assistants); data verification and management (Data Analyst/Manager); analytic consultant(s) specific to distinct methodological areas, including path analysis and econometrics (e.g., health economist); and additional computational resources, as needed.

#### **4.9 General Approach to Data Analysis**

##### **Quantitative Data Structure**

The data structure for the quantitative analyses is outlined in Table 2 below (which presents the general structure of this data file for a single participant [case 01] who is assumed to have been interviewed in each of the five waves of data collection). The first row (shaded) shows the structure of the baseline study used for cross-sectional analyses. The five rows taken together represent the repeated data over the course of the study period. All analyses will be based on an intent to treat.

**Table 2: Structure of the RCT Longitudinal Quantitative Data**

| Case ID | Time     | Stable Covariates | Time-Varying Covariates | MH/SA Status | Homelessness Status | Service Utilization |
|---------|----------|-------------------|-------------------------|--------------|---------------------|---------------------|
| 01      | Baseline | X                 | $Y_1$                   | $Z_1$        | $H_1$               | $S_1$               |
| 01      | 6 mos    | X                 | $Y_2$                   | $Z_2$        | $H_2$               | $S_2$               |
| 01      | 12 mos.  | X                 | $Y_3$                   | $Z_3$        | $H_3$               | $S_3$               |
| 01      | 18 mos.  | X                 | $Y_4$                   | $Z_4$        | $H_4$               | $S_4$               |
| 01      | 24 mos.  | X                 | $Y_5$                   | $Z_5$        | $H_5$               | $S_5$               |

**Definitions:**

**X** = A vector of variables and/or indicators representing individual characteristics whose values do not change over time. Examples include gender, age at entry, race/ethnicity and group intervention.

**$Y_i$**  = A vector of variables and indicators whose values at baseline may need to be repeatedly updated. Examples are psycho-social indicators such as family structure, income, indicators of social capital (family, marital status and social network indicators), human capital (schooling and employment status), indicators of resiliency (sense of coherence) and other events (e.g., a serious illness or injury) that occurred in the 6 months prior to the  $i^{th}$  interview.

**$Z_i$**  = A vector of indicators of alcohol, drug and mental health status as of the  $i^{th}$  interview. The time frame for these measures extends from “past week” or “last 30 days” to “last 6 months”.

**$H_i$**  = A vector of indicators of housing circumstances in the 6 months prior to the  $i^{th}$  year interview. See the discussion of these measures under Aim 1 below.

**$S_i$**  = A vector of indicators of services used during the 6 months prior to the  $i^{th}$  interview. These include services connected to receipt of the interventions (e.g., substance abuse treatment or work programs). These data will consist of information from records as well as self-reports.

**Quantitative Data Analysis**

In its most basic form, each RCT can be viewed as a mixed-effects 2 by 5 model (or in the case of the high needs group, a 3 by 5 model) with a number of different outcome measures of interest based on specific hypotheses (see section 2.3 for the outcome measures) and a number of potential covariates. The hypotheses address comparisons of specific sub-groups within the overall model.

The general analysis plan proposes several broad strategies of data analysis that will build upon the data as it is collected over the study period. The approach to analysis will begin with a baseline examination of the distribution of key factors across each sub-group. This univariate comparison of the distributions of key individual characteristics (e.g., demographic characteristics, substance abuse and mental health indicators) across each RCT sub-group will provide for an assessment of the effectiveness of the randomization process as well as identification of potential confounding factors that need to be accounted for in further analyses. Preliminary steps for all analyses will also involve assessing bivariate cross-tabulations and correlation matrices for relationships among variables. All variables will be checked with regard to their distribution (e.g., for normality and departures from normality) using frequency distributions, scatter plots and histograms. Statistics such as means, standard deviations, ranges, modes, medians and estimates of skewness and kurtosis will be computed.

We propose to assess our primary and secondary hypotheses using two approaches. The first (and simplest) is to perform cross-sectional analyses at each of the five measurement points (baseline, 6 months, etc.) comparing the 5 distinct intervention groups on the measure of interest at each point in time. Depending on the measure, this can be done using a non-parametric comparison for the categorical measures such as physical health status or parametric comparison (with confidence intervals) for the continuous measures (such as number of days housed). Plotted over time, this approach can provide a straight-forward and visual assessment of the relationship between the various interventions and the outcomes of interest. This approach, however, does not take into account the role of time or the variation within-groups over time specified in the hypotheses. Thus, we propose to conduct a number of longitudinal repeated measures analyses with the choice of the exact model depending on the intent of the individual hypotheses. We will begin with Generalized

Estimating Equations (GEE), adding in the specific interaction terms of interest as specified in the various hypotheses. This approach is based on specific assumptions around the pattern of missing data and will be adjusted as need be. An alternative approach is in the assessment of individual trajectories and draws from random effects models. Random effects models allow for a measure of variability in individual trajectories around the average group trajectory and are especially useful when it is reasonable to think of individual trajectories as a sample from the population of homelessness trajectories. All models will be implemented utilizing software applications which have the capability of modeling complex error structures at both the across individual (e.g., each person has their own trajectory of homelessness) as well as the within-individual (e.g., auto-correlated error structures of individuals' responses within their across time homelessness trajectory) levels.

**Analytic Limitations:** *Missing Data.* A concern throughout the analyses is the effect of missing data due to item non-response as well as panel attrition. In the case of missing data due to item non-response among persons who participate in a cycle of data collection, we plan to implement imputation methods, particularly for critical variables utilized in the cross-sectional presentation of the results. In general, we will use multiple imputation methods (Rubin, 1987) involving MCMC simulations. Available methods (Rubin, 1987) will be used to combine analysis results from multiple imputations that incorporate the uncertainty due to item non-response in the estimates of parameter variances. Models based on GEE (or related) approaches do not require the estimation of missing data.

*Panel attrition.* This is often more influential than item non-response on the comparison of groups. We will begin with a comprehensive investigation of baseline characteristics associated with patterns of participation will be examined by study follow-up wave to help identify the characteristics associated with trends in participation over time. Variables found to be significantly associated with attrition will be included as covariates in the models.

*Power considerations.* In light of the well-defined criteria established by the MHCC surrounding the sample size of each intervention arm as well as the understanding that the MHCC criteria takes account of panel attrition, no power calculations were conducted within the context of this application.

*Administrative Data.* The administrative data will be linked and incorporated with the quantitative data based on the appropriate vector of variables (see Table 2 above). Quantitative data analyses will be conducted drawing from these data in the same manner as that of data collected in the study.

**Qualitative Data.** We will begin constructing the qualitative database by entering and coding field notes, and transcribing the audio-taped interviews using NUD.IST and/or NVIVO software. One of the PIs (JF) has extensive experience in qualitative data analyses and has successfully used this software in prior studies. Simultaneous and iterative conduct of data collection and coding is central to qualitative research as it allows investigators to take advantage of insights that emerge during the course of fieldwork (Strauss, 1987). As data accumulates, the coding scheme will change to reflect the generation of new insights and the accumulation of increasingly detailed information. Thus, the outline presented above is an initial coding scheme that will change and expand over the course of the project.

Once we have identified and coded field note and interview data, the next step in analysis will be to distinguish repeated patterns from idiosyncratic individual statements and actions. This will be done by identifying which codes appear only infrequently in our database and which recur in a wide variety of interview transcripts and field notes. To enhance reliability, multiple analysts will examine the content of coded statements to ensure their accuracy and coding discrepancies will be identified

and addressed. Conducting analysis simultaneously with ongoing fieldwork will allow us to follow up on important statements, observations, and behaviors in later interviews and fieldwork (Glaser & Strauss, 1967). As observations and interviews progress, we will compose analytic memos that summarize the in-progress findings in the qualitative database, and help to identify areas for ongoing fieldwork. As the database grows, we will begin to identify similarities and differences across service settings and different groups of participants in the study.

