2. **Full Screening:** If pre-screening criteria are satisfied, participants will be asked the full set of screening questions. This will include evaluation of full inclusion and exclusion criteria, including classification as high or moderate need. Classification as *high*-need will correspond to Section 3 of Ontario Standards for ACT, as set forth by the MHCC. Classification as *moderate*-need will also be based on the same criteria; however, participants will be excluded if their score on the Symptom Checklist-90-R exceeds a threshold (to be determined) appropriate for the ICM condition. The

proportion of potential participants who fall into the high vs. moderate needs groups will be tested empirically during the implementation phase of the project.

Screening will be computer-based and will inform the interviewer whether or not the participant meets the study inclusion criteria as well as their level of need. Participants will be asked to return to the field office the following day to complete the **baseline evaluation** and then to receive notification of group assignment. In order to facilitate follow-up, participants will be asked to provide locations/ services they frequent regularly. This requirement to return the following day may pose a barrier to recruitment and recruiters will be trained to actively seek people who do not return.

**Randomization** will be performed separately for the two need groups (high and moderate). To control for initial differences among groups, randomization strata will include with or without substance use problems and absolute homelessness or precariously housed. Randomization will be performed using a block technique with variable block size using prepared tables. When participants return the next day to complete the baseline evaluation, they will receive notification of group assignment in a sealed envelope along with an information package; at this time, a field office worker will accompany participants who are assigned to an active intervention to the service provider's location. Those randomized to TAU will be informed about available services in the community. All participants will be invited to use the field office as a resource centre.

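### Covariates are to be picked from observed baseline differences and observed dropout, while the randomisation strata and the baseline outcome are not fixed as covariates: precision is lost and the adjusted model is not set in advance.

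*Protocol*

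**What the plan says.** Protocol section 4.3 (Randomization) randomises the high-need and moderate-need groups separately and stratifies within each: "randomization strata will include with or without substance use problems and absolute homelessness or precariously housed".

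Section 4.9 (Quantitative Data Analysis) describes each trial as a "mixed-effects 2 by 5 model (or in the case of the high needs group, a 3 by 5 model", with "a number of potential covariates" that are not listed. It begins from baseline: "This univariate comparison of the distributions of key individual characteristics" across arms "will provide for an assessment of the effectiveness of the randomization process" and leads to "identification of potential confounding factors that need to be accounted for in further analyses". Each hypothesis is then addressed in two ways: a separate comparison of arms at every measurement point, and longitudinal models (GEE first, random effects as an alternative).

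The paragraph on panel attrition in the same section adds a second rule: "Variables found to be significantly associated with attrition will be included as covariates in the models".

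Nowhere in section 4.9 are the two stratification factors put into a model. Baseline outcome values appear as the first row of the five-wave data structure (Table 2), not as a covariate.

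**The concern.** Under sound randomisation, differences between arms at baseline are chance. An observed imbalance does not show that a variable predicts the outcome, and prognostic strength is what makes adjustment worthwhile. A rule that turns observed differences into adjustment variables makes the effect estimate depend on which differences happen to appear. The attrition rule goes further, because the model cannot be known until dropout has been observed.

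The rule also tends to miss the variables the design itself marks as important. Stratified factors are balanced by construction, so a search for imbalance will almost never pick them. The baseline value of a symptom score, usually a strong predictor of its later value, would be picked only when it happened to differ between arms. What is at stake is efficiency in arms of fixed size, standard errors that match the design, and a primary model that can be written down before the data are seen.

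**Working it through.** **Inputs from the protocol.** 500 participants (section 5.1) in five groups. Section 4.6.1 samples 20 per group as 20% of participants, so 20 / 0.20 = 100 per group, and 5 × 100 = 500. The primary outcome variable is binary housing status at 2 years (section 4.6.2.1). Symptom number and severity form primary hypothesis 2 (section 4.1). Section 4.9 states that no power calculation was done, so there is no design figure to reproduce.

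**Assumptions (not in the protocol).** Two-sided 5%; 80 evaluable per arm; effect 0.4 SD; baseline to 24-month correlation r of 0.5 to 0.6, with 0.3 as a low case; normal approximation.

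**1. Value of the baseline outcome, continuous score.** Power = Φ(0.4 / √(2f/80) − 1.96), where f is the variance factor: 1 for a 24-month comparison ignoring baseline, 2(1 − r) for change from baseline, 1 − r² with baseline as covariate.

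| r | Ignoring baseline | Change from baseline | Baseline as covariate |
|---|---|---|---|
| 0.3 | f = 1.00; 72% | f = 1.40; 57% | f = 0.91; 76% |
| 0.5 | f = 1.00; 72% | f = 1.00; 72% | f = 0.75; 83% |
| 0.6 | f = 1.00; 72% | f = 0.80; 81% | f = 0.64; 89% |

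Example at r = 0.5 with baseline as covariate: 0.4 / √(1.5/80) = 2.921; 2.921 − 1.96 = 0.961; Φ = 0.83. The middle column represents the between-arm change contrast from a group-by-time model whose baseline means are left free.

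**2. Does adjusting only after an observed imbalance recover this?** Simulation with 20,000 replicates, 100 per arm, effect 0.396 SD (80% power unadjusted), and an assumed trigger of p < 0.05 on the baseline score.

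| r | Power, triggered | Power, always adjusted | Type I error, triggered |
|---|---|---|---|
| 0.3 | 80% | 83% | 0.046 |
| 0.5 | 81% | 90% | 0.042 |
| 0.7 | 82% | 97% | 0.035 |

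The trigger fires in about 5% of replicates, so almost all of the gain is lost. Type I error goes below 5%, not above it.

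**3. Leaving out the strata.** Let the strata explain a share R² of outcome variance (assumed). Stratified allocation makes the true variance of the contrast proportional to 1 − R², but an unadjusted model estimates it as 1. Type I error = 2[1 − Φ(1.96 / √(1 − R²))]. Power is at 100 per arm and 0.396 SD.

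| R² | Type I error, ignored | Power, ignored | Power, adjusted |
|---|---|---|---|
| 5% | 0.044 | 81% | 82% |
| 10% | 0.039 | 81% | 84% |
| 20% | 0.028 | 83% | 88% |

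**4. How easily chance supplies a confounder.** If k independent variables were screened at 5% under perfect randomisation, P(at least one) = 1 − 0.95^k: 40% for k = 10 and 64% for k = 20. With pairwise correlation 0.3 the figures are about 35% and 54%; with 0.5, about 29% and 42%. Neither k nor the 5% threshold is in the protocol, so this only illustrates how such a screen behaves.

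**The case against.** **No test of balance is stated.** This stands. Section 4.9 speaks of comparing distributions and gives no test or threshold; significance is named only in the attrition rule. A reader might infer that baseline balance will be tested at 5%, but the document does not say so. Selection by eye would still depend on the data.

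**Baseline is already in the models.** This stands in part. It is wave 1 of the 2 by 5 and 3 by 5 models, so it would be wrong to say that it is unused. As a free response it gives the change contrast, which is less precise than using it as a covariate at every correlation shown.

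**Covariate lists belong in a statistical analysis plan.** That would answer mere silence. Here the protocol states two selection rules, and those are what need changing.

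**Adjusting for predictors of dropout is legitimate.** This stands. Conditioning on baseline predictors of missingness is a recognised way to support GEE when dropout depends on covariates. The difficulty is choosing them by significance after the fact, not using them.

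**Analysts are blind to arm codes (section 4.3, Blinding).** This limits deliberate selection. It does not remove dependence on the data.

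A reader might also infer that false positives are inflated. The calculations do not support that: both the triggered adjustment and the omission of strata are conservative.

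**Conclusion.** The concern holds as a matter of efficiency and of fixing the model beforehand. The two rules in section 4.9 leave the adjusted model to chance imbalance and observed dropout, and they are unlikely to bring in the strata or, reliably, the baseline outcome. For a continuous score such as the SCL-90, under the stated assumptions, naming baseline as a covariate takes power from 72% (baseline ignored) or 72 to 81% (change contrast) to 83 to 89%. At a correlation of 0.3 it reaches only 76%.

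It would be tempting to read this gain across to the housing outcome. The protocol does not support that: every entrant is homeless or precariously housed (section 4.2), so baseline housing status probably varies little. There the strata are the relevant covariates, and their benefit is smaller and depends on how much of the outcome they explain. All power figures rest on assumed values, because the protocol gives none.

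**What to change.** In section 4.9, state that:

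- between-arm effect models adjust for substance use problems (yes/no), absolute homelessness versus precarious housing, and the baseline value of the outcome where it exists and varies. In the five-wave model, constraining baseline means to be equal across arms is an acceptable alternative to the baseline covariate;
- baseline tables are descriptive and do not select covariates;
- baseline predictors of attrition are named before unblinding and used in the imputation or weighting model, or as pre-named covariates in a sensitivity analysis.

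Keep the five-wave structure for the secondary hypotheses in section 4.1 that compare participants with their own baseline.

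The cost is wording only. The strata must be known for allocation, and baseline measures are already scheduled for all participants.
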